## Abstract

**Introduction:**

Clinically significant symptoms of depression and anxiety in coronary heart disease (CHD) patients are common and associated with adverse outcomes. Psychological treatments have shown limited effectiveness and more effective treatments have been requested. Attention training technique (ATT), a component of metacognitive therapy, can potentially be effective as a stand-alone treatment for anxiety and depression. In an open study, ATT delivered face-to-face in a group format was feasible and potentially effective for improving depression and anxiety symptoms in CHD patients. The next progressive step is to test the effectiveness of ATT in a randomized controlled trial. This paper describes the methodology of this trial.

**Methods:**

ATT-CHD is a randomized wait-list (WL) controlled study. Eligible CHD patients from two hospitals with Hospital Anxiety and Depression Scale (HADS)-Anxiety and/or HADS-Depression subscales scores ≥8 will be randomized into ATT (*n* = 32) or WL control (*n* = 32). After 6–8 weeks, WL patients will be allocated to ATT. Participants will be evaluated pre-, mid- and post-treatment, and at 6-months follow-up using changes in HADS as primary outcome. Secondary outcomes will be changes in psychiatric disorders, rumination, worry, type D-personality, metacognitions, insomnia, quality of life, and C-Reactive protein (CRP).

**Discussion:**

To our knowledge, this will be the first WL-controlled randomized study testing the effectiveness of group-based ATT as treatment of symptoms of anxiety and depression in CHD patients. It will also explore correlations between changes in psychological distress and CRP. A qualitative analysis will reveal patients’ experience with ATT including processes that may facilitate or serve as barriers to effectiveness. Recruitment into the study commenced in December 2022.

**Ethics and dissemination:**

The Regional Committees for Medical and Health Research Ethics (REK), Norway has granted approval for the study (ID 52002). The trial results will be published in peer-reviewed journals. According to Norwegian legislation, the Norwegian Data Protection Authority, and the Committee of Ethics, we are not allowed to share original study data publicly.

**Clinical trial registration:**

ClinicalTrials.gov, identifier NCT05621408 pre-inclusion. There were no significant changes of methods or outcomes after study start.

## Introduction

1.

Coronary heart disease (CHD) is one of the leading causes of death worldwide (Nowbar et al., 2019). Psychological distress such as significant symptoms of depression and anxiety are common in CHD patients (30–40%) (Reid et al., 2013) and commonly occur both immediate and longer periods of time after an acute cardiac event (Palacios et al., 2016). In an observational study from Norway, we reported prevalence rates of depression and anxiety of 14.7 and 21.1%, respectively, as assessed by the Hospital Anxiety and Depression Scale (HADS), mean 16.7 months after a CHD event (Frøjd et al., 2022b).

Patients with CHD have increased mortality risk with depression or anxiety alone being associated with up to two-fold increased risk of cardiovascular events and mortality (van Melle et al., 2004; Watkins et al., 2013). Depression and anxiety commonly co-occur and in those with both conditions, the prognosis is particularly poor with three-times increased risk of mortality (Watkins et al., 2013). Furthermore, associations between depression and anxiety have been reported for higher rates of cardiovascular risk factors, such as smoking and low physical activity, lower treatment adherence and higher levels of markers of immune function (Munkhaugen et al., 2018). The latter risk factor, more specific C-Reactive Protein (CRP), is an independent risk factor for recurrent cardiovascular events in CHD patients (Ridker et al., 2017). In addition, anxiety and depression symptoms are linked to poorer quality of life, higher rates of hospital admissions and work retention (Holdgaard et al., 2023).

Consequently, the most recent European Society of Cardiology guidelines on CVD prevention recommends assessments of psychological needs, including screening for anxiety and depression (Visseren et al., 2021). The importance of assessments of psychological distress in CHD and further intervention have been strongly emphasized (Thompson and Pedersen, 2023). However, a recent Cochrane review of studies on available drug and psychological treatments have showed only small effects on such symptoms and quality of life, and no effect on cardiac prognosis (Richards et al., 2017). Indeed, Richards et al. (2017) found no specific psychological intervention recommendable, and only small improvements in the interventions tested. More recently, Wells and colleagues reported metacognitive therapy (MCT) as a promising group delivered treatment in reducing psychological distress and improving quality of life in cardiac rehabilitation patients an evaluated their MCT interventions in cardiac patients (Wells et al., 2021, 2022a,b). Another recent multicenter RCT on cognitive-behavior therapy (CBT) in cardiac rehabilitation (CR) patients found that supplementing CBT to CR could improve anxiety, depression, quality of life as well as cardiac readmissions (Holdgaard et al., 2023). These effects were maintained at 6-months follow-up.

The attention training technique (ATT) is a component of metacognitive therapy, a treatment approach grounded in the metacognitive model (MCM) of psychological disorder (Wells, 2009). The MCM is based on the principle that particular transdiagnostic processes that represent biases in self-regulation of thinking are major contributors to psychological disorders. A central mechanism is sustained processing of threat and persistent negative ideation-focused coping typified by worry and rumination; a reactive style that is collectively termed the cognitive-attention syndrome or CAS (Wells and Matthews, 1994). The CAS is thought to emerge from biases in metacognition that includes the person’s knowledge and internal programs for regulating thinking and attention (Wells, 2009). Techniques such as the attention training are designed to facilitate the modification of such metacognitions and enhance attention flexibility such that an individual can choose not to engage in the CAS when negative cognitions occur. There is firm evidence that MCT is effective in treating depression and anxiety disorders (Normann and Morina, 2018), and potentially more effective than traditional CBT (Normann et al., 2014; Nordahl et al., 2018) and that individual techniques of MCT such as ATT, can be effective in their own right (e.g., Fergus and Bardeen, 2016).

ATT consists of an auditory attention task that takes about 12 min to practice (Wells, 2009). Consistent with predictions of the S-REF model, ATT has been found to increase attentional flexibility (Barth et al., 2019) and be effective for a range of different psychiatric disorders including symptoms of depression and anxiety as a stand-alone treatment (Fergus and Bardeen, 2016). Recently, RCTs have reported ATT delivered in group formats to be effective in reducing symptoms of anxiety and depression among a student population (Haukaas et al., 2018). There is also preliminary evidence from an open study that ATT is feasible and potentially effective in treating symptoms of anxiety and depression in CHD patients (Dammen et al., 2022).

In addition to improving symptoms of anxiety and depression, because of its mechanism of action, ATT may improve biological markers associated with CHD. Several reviews of the effects of psychological interventions on systemic levels of inflammatory biomarkers have concluded that psychological interventions appear efficacious in reducing CRP, for example, Savin et al. (2022) who reviewed studies of CBT for insomnia and (O'Toole et al., 2018) who included a broader range of therapies. However, no study has measured the effect of ATT on CRP-levels and the associations between distress symptom change and changes in CRP. Such knowledge might provide further evidence of the link between psychological distress and poor cardiac prognosis and has been required (Richards et al., 2017).

In summary, ATT is an effective approach in treating anxiety and depression in clinical and non-clinical populations and delivered individually and in group formats. ATT has potentially many advantages for its use in the CHD patient group. It is derived from a transdiagnostic model of emotional disorder, hence allowing disparate presentations to be addressed with the same core treatment approach. ATT aims to address underlying mechanisms which could represent obstacles to recovery in traditional therapies. It is easier to implement than traditional therapies because it does not require dealing with aspects of life or symptoms that are difficult for patients to confront during therapy. ATT does not require the same level of training and resources to administer as traditional psychotherapies. Instead, ATT consists of exercises that could be administered by trained general practitioners or cardiac nurses and it does not necessarily require a mental health therapist with training in specific therapies. This makes it particularly well suited to CHD patients who often present with mixed anxiety and depression. Finally, in a recent open study, we found ATT delivered face-to-face in a 6- session group format to be feasible and potentially effective for improving depression and anxiety symptoms in CHD patients (Dammen et al., 2022), which holds considerable appeal for use in increasingly busy cardiac follow-up clinics. The next progressive step is to test the effectiveness of ATT in a randomized controlled clinical trial. This study will investigate the effectiveness of ATT compared to a wait list control condition (WL). Those in the WL will also receive ATT after 6–8 weeks (“delayed ATT”). Changes from post treatment to 6 months after treatment will be reported for all treated patients and comparisons will be made at 6 months follow up for those who received “immediate ATT” and “delayed ATT.”

Furthermore, a qualitative study will be “nested” within this RCT. Including a qualitative approach will allow a greater focus on the perspective of the users. To our knowledge, no previous studies have explored how patients experience aspects of ATT delivered in a group format.

### Objectives

1.1.

The overall aim of this study is to provide evidence for the effectiveness of ATT delivered in a group format in CHD outpatients.

The primary objective is to test the effectiveness of ATT delivered in a group format in alleviating symptoms of anxiety and depression in CHD outpatients who experience significant anxiety and depression following a CHD event.

Secondary objectives are (i) to evaluate the impact of ATT on secondary outcomes such as psychiatric disorders, rumination, worry, type D-personality, insomnia, quality of life and metacognitions (ii) explore whether the biological marker CRP that may link psychological factors to cardiac prognosis is correlated with treatment outcome, and (iii) provide qualitative data on the patients experience with ATT including processes that may facilitate or serve as barriers to effectiveness in order to help further improvement in effective delivery and implementation of ATT in cardiac practice.

## Methods and analysis

2.

### Study design

2.1.

ATT-CHD is a multi-center single-blind waiting list randomized controlled trial with 6 months’ follow-up comparing ATT delivered in a group format with a wait-list control condition. Wait-list control condition is the chosen comparison arm because there is currently no benchmark treatment for distress in this group, existing treatments have limited effects, and this is the first test of group ATT in CHD patients. There are also qualitative evaluations embedded within the trial. A trial flow diagram is shown in Figure 1. An overview of assessments is provided in Table 1.

**Figure 1 fig1:**
[figure not shown]
CONSORT flow diagram.

**Table 1 tab1:** Assessments (measurement times are marked with a cross).

Week	SCRE	Pre	w1	w2	w3	w4	w5	w6	Post	Pre	w1	w2	w3	w4	w5	w6	Post	6 mo. FU
Inclusion/exclusion criteria																		
Informed consent																		
Socio-demographics																		
HADS																		
RRS																		
PBRS/NBRS																		
MCQ-30																		
DS-14																		
BIS																		
PSWQ																		
SF12																		
SCID-I/II																		
HsCRP																		

SCID, Structured Clinical Interview for DSM; RRS, Ruminative Response Scale; PBRS, Positive Belief About Rumination Scale; NBRS, Negative Belief About Rumination Scale; MCQ-30, Metacognitive Questionnaire−30; DS14, Type D Questionnaire; BIS, Bergen Insomnia Scale; DMQ, PWSQ, Penn State Worry Questionnaire; SF12, Short-Form−12; HADS, Hospital Anxiety and Depression Scale; hsCRP, high-sensitivity C-Reactive Protein; w, week; mo, month.

### Study setting

2.2.

The study will take place at two large general hospitals (Drammen and Vestfold) in Norway. The study is granted approval by the South-Eastern Norway Regional Health Authority (Helse Sør-Øst RHF/Grant number 2019125).

### Study population

2.3.

The study population will include patients previously hospitalized with myocardial infarction and/or angiography-verified atherosclerosis. The hospitals catchment area corresponds to 7.4 percent of the Norwegian population. It is representative of Norwegian geography, age distribution and morbidity (Kristiansen et al., 2021).

### Eligibility criteria

2.4.

Patients will be asked to participate in the study if they meet the following inclusion criteria:

Previously hospitalized with myocardial infarction and/or angiography-verified atherosclerosis.A score of ≥8 on the HADS-anxiety and/or depression subscales.Age ≥ 18 to ≤65 years.Ability to understand and speak the Norwegian language.Signed informed consent.

Patients will be excluded if they meet any of the following criteria:

Current or past neurological illness, traumatic brain injury.Current alcohol and/or substance dependency disorders.Psychotic disorders, bipolar disorders, developmental disorders or learning disabilities.Cognitive impairment which precludes informed consent/ability to participate.Acute suicidality.Life-expectancy less than 12 months.Concurrent psychological intervention for emotional distress.Antidepressant or anxiolytic medication initiated or changed during the past 8 weeks.

### Recruitment and allocation

2.5.

Consecutive patients hospitalized with a CHD event during the past years (2011–2022) at the department of cardiology at Drammen hospital or Vestfold hospital will be assessed for eligibility. All potentially eligible patients will be selected from hospital discharge lists by searching chronologically after last admission for the index event during the past years (2011–2022) prior to study inclusion. A specially-trained research cardiac nurse will screen the hospital records. All eligible patients (*N*⁓1,500) will be mailed a comprehensive self-report questionnaire as part of a follow up study addressing psychological distress. The responses will be screened by a research nurse and those who score ≥ 8 for HADS-A and/or HADS-D will be mailed information about the ATT-CHD study and consent to be contacted for further information and evaluation if they return a signed informed consent form together with a recent score ≥ 8 on either of the HADS subscales. Those who meet our eligibility criteria will be offered a face-to-face evaluation, and information about the study if eligible. Those who consent to participate will undergo diagnostic interviews as well as self-report assessments before being randomized and allocated to either ATT immediately or wait-list control. Randomization will be performed by a study statistician blinded to the results of the evaluations. An online software tool is used for randomization with a block- and list-size of 8–12 persons (Sealed Envelope Ltd, 2022. Create a blocked randomization list^1^). The randomization program will be kept in a secured, logged hard disk. Before randomization, baseline data will be collected (Table 1).

### Intervention: ATT provided in a group format

2.6.

ATT was developed by Wells (1990) with the aim of facilitating flexible control of attention. The protocol has been tested in anxiety disorders and in depression (e.g., Papageorgiou and Wells, 2000). The intervention will follow the protocol as described in Wells (2009) treatment manual. The participants will be introduced to the rationale for ATT and explanation of internal and external focus of attention. A rationale will further be given for how ATT may aid in shifting focus of attention and subsequently assisting in overcoming psychological distress. Consistent with Wells (2009), ATT was embedded within meta-level discourse during each session.

The treatment will consist of six weekly group sessions of 60–90 min duration. The number of sessions was based on the results of our feasibility study (Dammen et al., 2022) that is also in line with the number of sessions applied in group MCT study in cardiac patients by Wells et al. (2020). The first session will focus on an explanation of psychological distress in the context of CHD, self-focus of attention, rationale, and practice of ATT as a method of counteracting excessive self-focus. Participants will be informed that they can learn to let go of worry and rumination (overthinking) with the help of ATT. In line with the treatment manual (Wells, 2009), after the initial session, the structure of the sessions will be as follows: review of last session and homework assignment, ATT practice with scoring of self-focus of attention before and after, homework with ATT practice.

ATT is an auditory attention task that takes about 12 min to practice and will be provided to participants as CD or mp3/4 files. The ATT version is a Norwegian translation of the original Wells (2007) recording and has been used in previous studies (e.g., Dammen et al., 2015) with permission from the originator for the current study. After introduction and practice in session, the patients will be asked to perform ATT daily as a homework assignment and in-session practice of ATT will be used throughout the treatment. All patients will be encouraged to practice ATT twice a day as homework between the sessions during the first 3 weeks. Compliance and response to ATT will be recorded for each patient.

### Wait list control

2.7.

This will involve monitoring patients waiting to receive ATT for a period of 6–8 weeks. These patients may access on demand follow up consultation at general practitioners. At the end of this period, patients will be re-assessed prior to being allocated to receive group ATT.

### Training, supervision and treatment fidelity

2.8.

The therapist (TD) performing the treatment has completed Level 1 and 2 training in MCT, published studies on group metacognitive therapy in depressed patients (Dammen et al., 2015, 2016), and thus is familiar with ATT treatment. In order to maintain treatment fidelity, supervision will be provided by CP on a weekly basis. CP has received training from the originator of ATT. In addition, all sessions will be audiotaped and a random sample of 10% will be checked for therapist competence and treatment fidelity as rated by independent MCT experts using a checklist. Inter-rater Kappa coefficients for competency/fidelity ratings will be reported.

### Data collection: participant timeline

2.9.

Patients will complete measures at baseline, mid-treatment, post-treatment and 6 months follow up. Details are shown in Table 1. No financial compensation will be provided to the participants.

### Criteria for discontinuation of participants

2.10.

Participants may withdraw from the study at any time without any consequences and without giving any reasons. Participants who chose to withdraw will receive usual care. Patients can also be withdrawn at the request of the principal investigator if a participant is deemed to require other urgent treatment, e.g., hospitalization because of somatic illness or need of other specialist care.

### Outcomes

2.11.

Primary outcomes are: changes in HADS-anxiety and HADS-depression scores from pre-treatment to post-treatment and 6 months follow-up between treatment arms. Changes in the proportion of patients scoring below 8 on HADS-anxiety and HADS-depression, respectively, from pre-treatment to post-treatment and 6-months follow-up between treatment arms.

Secondary outcomes are changes in psychiatric disorders, rumination, worry, type D-personality, insomnia, quality of life and metacognitions scores, as well as CRP levels, from pre-treatment to post-treatment and 6-months follow-up between treatment arms. In addition, qualitative data will be collected and evaluated.

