### Sample size and power calculation

2.13.

Statistical power calculation was based on the primary outcome of HADS with subscale outcomes of HADS-depression and HADS-anxiety. A conservative anxiety/depression effect size from previous studies of individual and group ATT for depression was used (0.67). This effect size is similar to what has been reported in a meta-analytic study of CBT and other psychological treatments (0.67) (Cuijpers et al., 2010). Thus, based on previous research, we expected a difference between the two conditions (ATT and WLC) amounting to an effect size of approximately 0.67. Allowing for 15–20% drop out in accordance with previous studies, we aim for a final sample size of 32 in each group, i.e., 64 in total. This yields a statistical power above 90% using a two-sided significance test (*p* < 0.05).

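### The power figure rests on a standardised mean difference in HADS scores and does not hold for the proportions below 8 that are also listed as primary outcomes

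*Protocol article*

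**What the plan says.** Section 2.11 (Outcomes) opens its primary list with "Primary outcomes are: changes in HADS-anxiety and HADS-depression scores from pre-treatment to post-treatment and 6 months follow-up between treatment arms". The next sentence, still ahead of the secondary outcomes, adds "Changes in the proportion of patients scoring below 8 on HADS-anxiety and HADS-depression, respectively, from pre-treatment to post-treatment", and extends this to the 6-month follow-up. Counted by subscale, that makes four primary variables: two scores and two proportions.

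Section 2.13 (Sample size and power calculation) introduces its calculation with "Statistical power calculation was based on the primary outcome of HADS with subscale outcomes of HADS-depression and HADS-anxiety". The effect is "a difference between the two conditions (ATT and WLC) amounting to an effect size of approximately 0.67", the size is given as "we aim for a final sample size of 32 in each group, i.e., 64 in total", and the result as "This yields a statistical power above 90% using a two-sided significance test" at the 5% level. The attrition statement is "Allowing for 15–20% drop out in accordance with previous studies". The section names no proportion.

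Section 2.14.1 (Quantitative analysis) fits a linear mixed model to the HADS-A and HADS-D scores. It defines the controlled effect size as the post-treatment difference in means over the pooled standard deviation. No analysis of the proportions is named there.

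**The concern.** A comparison of two proportions is a different statistic from a comparison of two means. Cutting a score at 8 discards information, so a given shift in the score is harder to detect after the cut. A power derived from a standardised mean difference cannot be carried over to the proportions. Section 2.13 nevertheless ties its single figure to the primary HADS outcome without restriction, while section 2.11 counts the proportions as part of that outcome.

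The practical risk is mixed results. If ATT works as well as assumed, a significant score could easily appear beside one or two non-significant primary proportions. A reader relying on the printed power would have no warning that those misses were likely even with a true effect.

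**Working it through.** **Inputs from the article.** Effect 0.67 SD, 32 per arm, two-sided 5%, dropout 15–20% (section 2.13). The Methods paragraph of the abstract gives 32 per arm as the number randomised, so dropout leaves 32 × 0.85 = 27.2 to 32 × 0.80 = 25.6, about 27 to 26 evaluable per arm.

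**Assumed, because the article does not give them.** The wait-list proportion below 8 after treatment (p0) is 10–60%. The underlying score is normal or, as a variant, logistic. The comparison is cross-sectional at post-treatment.

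**Step 1: the plan's own figure, for the scores.** The noncentrality is 0.67 × √(32/2) = 2.68. Normal approximation: Φ(2.68 − 1.96) = 76.4%. Noncentral t: 75.1%. The printed figure of above 90% is not reproduced, even for the scores.

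**Step 2: turn 0.67 SD into two proportions.**
- Normal score: p1 = Φ(Φ⁻¹(p0) + 0.67). Example: p0 = 0.30 gives Φ(−0.524 + 0.67) = Φ(0.146) = 0.558.
- Logistic score: odds ratio exp(0.67 × π/√3) = 3.37. Example: p0 = 0.30 gives odds 0.4286 × 3.37 = 1.445, so p1 = 0.591.

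**Step 3: power by exact binomial enumeration, 32 per arm, two-sided 5%.**

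| p0 | p1 normal | chi-square | Fisher | p1 logistic | chi-square | Fisher |
|---|---|---|---|---|---|---|
| 10% | 27.0% | 42.8% | 30.6% | 27.2% | 43.5% | 31.3% |
| 20% | 43.2% | 52.7% | 42.7% | 45.7% | 60.8% | 50.9% |
| 30% | 55.8% | 58.3% | 48.0% | 59.1% | 68.7% | 59.0% |
| 40% | 66.2% | 59.3% | 49.1% | 69.2% | 69.0% | 59.3% |
| 50% | 74.9% | 55.8% | 45.5% | 77.1% | 63.7% | 53.7% |
| 60% | 82.2% | 51.4% | 41.3% | 83.5% | 56.8% | 46.6% |

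Hand check at p0 = 0.30, normal score, pooled approximation: the difference is 0.258, the null standard error √(2 × 0.429 × 0.571/32) = 0.1237, and the alternative standard error √((0.210 + 0.247)/32) = 0.1195. Then (0.258 − 1.96 × 0.1237)/0.1195 = 0.13, and Φ(0.13) = 55%, close to the exact 58.3%.

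**Step 4: after dropout, 26 per arm.** Normal score: chi-square 38–48%, Fisher 24–37%. Logistic score: chi-square 38–56%, Fisher 25–46%.

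**Step 5: would repairing the score power repair the proportions?** With 32 per arm the score t-test reaches about 90% at a standardised effect of about 0.82. At 0.82, with p0 from 20% to 50%, the proportions reach 71–76% by chi-square for a normal score and 78–85% for a logistic one. Both remain below the score.

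**The case against.** The strongest reply is that the article never prints a power for the proportions. Section 2.13 speaks of an effect size on the subscales, section 2.14.1 defines that effect on the mean scale and models the scores, and the abstract names change in HADS as primary. A statistician would take the figure as belonging to the scores, and sizing on the continuous measure is common. This is fair as far as it goes: no printed figure for a proportion is wrong. What remains is a mismatch between sections, because 2.11 calls the proportions primary and 2.13 does not limit its statement. The sentence on proportions has no verb, but its place between the primary and secondary lists leaves its status in little doubt.

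A second reply is that the mixed model may use baseline scores and so gain power. For the scores, adjustment would reach 90% with 32 per arm only at a pre–post correlation of about 0.59 or more, and the article states none. A gain there would not carry over to an unadjusted comparison of proportions. False discovery rate control does not help either, since it addresses false positives.

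Third, the power range depends on the model. This stands. A reader might take 59% as a ceiling, or conclude that the cut always costs at least 16 points (75 − 59). The logistic variant reaches about 69%, a loss of about 6 points, so neither holds in general. A reader might also set the proportions against the printed 90% and claim a loss of 30 points or more. About 15 of those points (90 − 75) come from the separate error in the score power. Nor does any text show that the investigators would read a non-significant proportion as evidence of no effect.

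**Conclusion.** The point holds as an inconsistency between what is declared primary and what the power statement covers. Under the article's own 0.67 SD and 32 per arm, power for each proportion is about 43–59% by chi-square with a normal score, up to about 69% with a logistic score, and about 31–59% by Fisher's exact test across both. It is lower after the stated dropout. The direction is the same in every case examined; the exact loss is not fixed, because it depends on the assumed 10–60% wait-list proportion and on the shape of the score. The comparator is about 75% for the score t-test, not the printed 90%, and correcting that figure would not by itself settle the matter for the proportions. The score comparison remains a valid primary analysis, so this should be corrected but does not undermine the trial.

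**What to change.** In section 2.13, state that the power figure, itself to be corrected, applies only to the comparison of continuous HADS scores, and that the proportions below 8 are not powered at that level. In section 2.11, move the proportions to secondary or supportive status, reported as between-arm risk differences with 95% confidence intervals to help interpret the score result.

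No patients or data are added. It is more than a wording change, though. The first patient was randomised in November 2022, and the article reports no significant change of outcomes since the start. The reclassification therefore needs a dated protocol and registry amendment, with its reason, before any unblinded analysis. The price is a documented mid-trial reclassification and the loss of any confirmatory claim on the cut-off.
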